## 1. Scope of this document

This analysis plan deals only with the statistical analysis of feasibility and efficacy; any planned cost-effectiveness analysis will be detailed in a separate document. This analysis plan was written prior to the completion of three-month data collection. The BASIL pilot study will follow patients up for twelve months, but this analysis plan will only detail the analysis of data up to and including the three-month timepoint. Analysis of the twelve-month data will be included as a future addendum in the future.

## 2. Definition of terms/acronyms

|         |                                                  |
|---------|--------------------------------------------------|
| AE      | Adverse Event                                    |
| BA      | Behavioural Activation                           |
| BASIL   | Behavioural Activation for Social Isolation      |
| C19     | COVID-19                                         |
| CONSORT | Consolidated Standards of Reporting Trials       |
| CRF     | Case Report Form                                 |
| GAD-7   | Generalised Anxiety Disorder (Assessment)-7 item |
| ICC     | Intraclass Correlation Coefficient               |
| LTC     | Long Term Condition                              |
| NHS     | National Health Service                          |
| PHQ-9   | Patient Health Questionnaire-9 item              |
| RCT     | Randomised Controlled Trial                      |
| SAE     | Serious Adverse Event                            |
| SF-12v2 | Short Form-12 item                               |
| UK      | United Kingdom                                   |
| YTU     | York Trials Unit                                 |

## 3. Design

BASIL-C19 is a two-arm parallel group individually randomised controlled pilot trial with an embedded qualitative process evaluation. The two trial arms are: Behavioural Activation (BA) within a collaborative care framework; and care as usual as provided by the participant's current NHS and/or third sector health care providers, in addition to signposting information to reputable sources of support on maintaining physical and mental wellbeing. Randomisation is conducted at the individual patient level, and the trial aimed to recruit 100 participants.

Full details of the background and design of the trial are presented in the protocol (version 4.0).

## 4. Trial Objectives

The aims of BASIL-C19 are to:

1. Use a manualised BA focussed collaborative care intervention and practitioner training package for older adults with multiple health conditions who are following UK government social distancing and isolation guidelines due to Covid-19.
2. Establish procedures for recruitment, randomisation, and retention for a definitive trial.
3. Establish an acceptable and deliverable range of assessment procedures for a definitive trial.
4. Estimate parameters for the sample size for a definitive trial.
5. Assess acceptability of the intervention for Covid-19 induced social isolation/self-isolation.

## **5. Sample Size**

The primary aim of the BASIL-C19 pilot RCT is to test the feasibility of the intervention and the methods of recruitment, randomisation, and follow-up. Sample size calculations are based on estimating attrition and standard deviation of the primary clinical outcome. We proposed to recruit 100 participants. The intervention will be delivered by support workers and we can allow for potential clustering by support worker assuming an intracluster correlation coefficient (ICC) of 0.01 and an average cluster size of 15. The effective sample size is therefore 88. Assuming 15-20% of participants are lost to follow-up (17% in the CASPER trial of older adults[1]), we should have an effective sample size of at least 70 participants. This will allow a completion rate of 80% to be estimated within a 95% confidence interval of  $\pm 8\%$  and reasonably robust estimates of the standard deviation of the primary clinical outcome measure to inform the sample size calculation for a definitive trial[2].

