## **8.2 Patient Reported Outcomes**

Patient reported outcomes (PHQ-9, GAD-7, De Jong Gierveld Scale, SF-12v2) at baseline, one and three months will be summarised by group. Mean and standard deviation with the number of observations used in each calculation, will be presented (Table 3). In addition, participant's circumstances regarding Covid-19 will be summarised by group for each time point.

Linear regression will be used to explore differences in the PHQ-9 and De Jong Gierveld Loneliness Scale, adjusting for the baseline measure of the score, between groups at one-month and three-months. The mean difference and a 95% confidence interval will be provided. Model assumptions will be checked prior to analysis.

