## **8.5 Analysis of main trial sub-population**

For the main trial (BASIL+) the inclusion criteria requires a score of  $\geq 5$  on the Patient Health Questionnaire (PHQ-9) at screening, thereby targeting people at risk of clinical depression or with already established depressive symptoms. This criterion emerged from the early experience in the pilot trial where the research team observed that people with very low scores on the PHQ9 did not engage as well with the intervention. We implemented this inclusion criteria for the planned main trial (anticipated recruitment start date February 2021: <http://www.isrctn.com/ISRCTN63034289>). It is with this in mind that the linear regression for the PHQ-9 will be repeated for the subpopulation in the pilot trial that would be eligible for the main trial (i.e. those with a screening PHQ-9 score of five

or more). From these linear regression, 80% confidence intervals for the mean difference will be presented.

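### The SAP plans PHQ-9 standard deviations only for the full pilot sample, although the main trial takes only people with screening PHQ-9 of 5 or more; the ±8% in Section 5 also does not follow from an effective sample of 70

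*SAP*

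**What the plan says.** Section 4 lists as its fourth aim: "Estimate parameters for the sample size for a definitive trial". Section 5 bases the pilot's size on two quantities, attrition and the SD of the primary clinical outcome, which Section 7.1 defines as PHQ-9 at one month. It starts from "We proposed to recruit 100 participants", allows for clustering by support worker "assuming an intracluster correlation coefficient (ICC) of 0.01 and an average cluster size of 15", and concludes: "The effective sample size is therefore 88". It then continues "Assuming 15-20% of participants are lost to follow-up" and arrives at an effective sample of at least 70. The next sentence refers back to that 70 and promises two things: an 80% completion rate estimated to within ±8%, and "reasonably robust estimates of the standard deviation of the primary clinical outcome measure to inform the sample size calculation for a definitive trial". The first promise has a figure. The second has a citation but no figure.

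For the analysis, Section 8.2 says: "Mean and standard deviation with the number of observations used in each calculation, will be presented (Table 3"). The outcome table shell in the appendix has the same content: n, mean and SD for each arm at each time point. The only interval in 8.2 is a 95% interval for the baseline-adjusted mean difference.

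Section 8.5 explains that the main trial requires a screening PHQ-9 of 5 or more. For that reason "the linear regression for the PHQ-9 will be repeated for the subpopulation in the pilot trial that would be eligible for the main trial". The stated output is the mean difference with an 80% interval.

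**The concern.** The pilot is meant to supply the variance that sizes the main trial. Section 8.5 shows that the authors already know the main trial's population is a selected part of the pilot's. The SAP carries that knowledge into the treatment comparison but not into the SD. Followed as written, it gives an SD that includes people the main trial will exclude, and none for those it will include.

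Selection on screening PHQ-9 can change the spread of the follow-up score and its correlation with baseline. A required sample size is proportional to the square of the SD, so any gap between the two SDs enters squared. Baseline adjustment matters as well: 8.2 and 8.5 compare PHQ-9 after adjustment, and a main trial analysed that way would need the residual SD, or the raw SD together with the correlation. None of these is planned as an output.

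The completion-rate figure is a smaller matter, but it stands in the same sentence and overstates what an effective 70 can deliver.

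**Working it through.** **Inputs (SAP Section 5 unless noted).** Recruitment 100; ICC 0.01; average cluster size 15; loss 15–20%; completion rate 80%; 1:1 allocation (Section 6).

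**Step 1: the plan's sample sizes.**
- Design effect: 1 + (15 − 1) × 0.01 = 1.14.
- Effective size before loss: 100 / 1.14 = 87.7, stated as 88. Reproduced.
- After 20% loss: 88 × 0.80 = 70.4, stated as at least 70. Reproduced. After 15% loss: 88 × 0.85 = 74.8.

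**Step 2: the ±8%.** Half-width = 1.96 × √(0.8 × 0.2 / n).

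| n | What it is | Half-width |
|---|---|---|
| 100 | all randomised | ±7.8% |
| 88 | effective size before loss | ±8.4% |
| 70 | effective size after loss | ±9.4% |

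A half-width of 8% needs n = 1.96² × 0.16 / 0.08² = 96. The figure fits 100, or 88 after rounding. It does not fit 70, the number to which the sentence attaches it.

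**Step 3: which SDs are planned.**

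| Quantity for PHQ-9 | Full sample (8.2 and table shell) | Screening PHQ-9 ≥ 5 (8.5) |
|---|---|---|
| SD by arm, with n | planned | not planned |
| Pooled within-arm SD | not planned, but follows from the arm values | not planned |
| Residual SD after baseline adjustment | not planned | not planned |
| Baseline-to-follow-up correlation | not planned | not planned |
| Mean difference with interval | planned (95%) | planned (80%) |

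**Step 4: precision of an SD.** For roughly normal data the 95% limits are the estimate times √(df / χ²), with χ² at its 0.975 and 0.025 quantiles. Squaring them gives the range for a required sample size N.

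| Basis | df | SD limits (× estimate) | N (× estimate) |
|---|---|---|---|
| Pooled, effective 70 | 68 | 0.86 to 1.20 | 0.73 to 1.44 |
| Pooled, 80 observed completers | 78 | 0.86 to 1.19 | 0.75 to 1.41 |
| Subgroup of 49, pooled (assumption: 70% of 70) | 47 | 0.83 to 1.25 | 0.69 to 1.57 |
| Subgroup of 35, pooled (assumption: 50% of 70) | 33 | 0.81 to 1.32 | 0.65 to 1.73 |

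The subgroup's share is not in the document, so the last two rows only illustrate the direction. If PHQ-9 is right-skewed, the true intervals are wider. In simulation with 35 per arm, the central 95% range of the pooled estimate relative to the true SD was 0.83 to 1.17 for near-normal data and 0.79 to 1.23 for a gamma distribution with excess kurtosis 1.5.

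**The case against.** **Much can be recovered from what is planned.** With n and SD by arm, a reader can compute the full-sample pooled SD and its interval. The width of the 95% interval for the adjusted difference, with the arm sizes, gives the residual SD approximately. This stands: in the full sample the additions are mostly a convenience. In the subgroup, the 80% interval would give an approximate residual SD only if the numbers by arm are reported, and 8.5 does not commit to that. The raw SD and the correlation there cannot be recovered.

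**The effective 70 may be too pessimistic for an SD.** The design effect concerns the precision of a mean, and the SD would come from the 80–85 people actually observed. Support workers deliver only the intervention, so deflating that arm alone would leave (50 + 50/1.14) × 0.80 = 75. This also stands, but it moves the interval little, as the 78 df row shows.

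**Whether the SD is adequate depends on the cited simulation study.** That source is not at hand, so nothing here says the phrase about robustness is false or that 70 is too few.

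**A reader might infer that a main trial sized from this SD has an even chance of being too small.** The chance that a sample SD falls below the true one is 0.523 at 68 df, but it is still 0.511 at 300 df and 0.506 at 1000 df. It is a property of any point estimate of a variance and shows no fault in this plan. The SAP also says only that the SD will inform the calculation, not that the raw value will be used. Nor does it follow that the main trial must be sized from an upper confidence limit. That choice belongs to the main trial's own documents.

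**Conclusion.** The point holds in this form. The variance for the main trial is a core product of the pilot, the main trial's population is defined in 8.5, and the SAP plans no SD for that population. The document gives neither the size nor the direction of the resulting error. The intervals in the working rest on approximate normality, and the subgroup rows on an assumed share of 50–70%. The need for a residual SD assumes that the main trial also adjusts for baseline, as this SAP does.

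The completion-rate figure is wrong as attached: ±9.4% at 70, against the stated ±8%. The likely explanation is that it was computed on those randomised, which is the natural denominator for a completion rate.

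Neither matter invalidates a pilot result. Both concern how well Section 4's fourth aim and Section 5's promise are met. Section 8.5 describes the main trial as already planned; if its size is already fixed, the same outputs serve as a check on it.

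**What to change.** - **Section 8.5:** for PHQ-9 at one and three months among those with screening PHQ-9 of 5 or more, add the n by arm, the pooled within-arm SD, the residual SD from the baseline-adjusted regression and the baseline-to-follow-up correlation. Give the SDs and the correlation with 95% intervals.
- **Section 8.2 and the table shell:** add the same quantities for the full sample.
- **Section 5, SD:** put a figure beside the phrase on robustness, for example a 95% interval of about 0.86 to 1.20 times the SD at an effective 70, and note that it will be wider in the subgroup.
- **Section 5, completion rate:** either give ±9.4% for 70, or give ±7.8% and state that the denominator is all 100 randomised (±8.4% if the effective 88 is meant).

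The cost is a few lines of SAP text and some extra output from data and regressions already planned. No patients or measurements are added. The downside is that the stated precision looks slightly less favourable.

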## **6. Randomisation**

Eligible and consenting participants were randomised using simple randomisation on a 1:1 basis to either the intervention group (BA) or the usual care with signposting group following completion of the baseline questionnaire. A statistician at the York Trials Unit (YTU), not involved with the recruitment of participants, generated the allocation schedule. Randomisation was carried out by YTU's secure randomisation service and participants informed of their group allocation by telephone (confirmed via letter/email).

## 7. Outcomes

### 7.1 Primary outcome(s)

As this is a pilot study, the primary outcomes will be related to feasibility, including screening, recruitment, and follow-up rates and delivery of the intervention (number, and duration, of intervention sessions attended).

The primary clinical outcome measure is self-reported depression severity (as measured by the PHQ-9) at one-month post-randomisation. This measure is widely used in clinical trials and settings, provides excellent internal and external validity, and has established specificity/sensitivity in a UK population. We have chosen one month as the primary outcome timepoint to enable us to test whether the intervention mitigates depression during the period of social isolation/self-isolation.

### 7.2 Other patient-reported, secondary outcomes

The following patient-reported outcome measures are completed at baseline, one, three-, and 12-months post-randomisation:

- **Patient Health Questionnaire-9 (PHQ-9)** – The PHQ-9 is the 9-item depression module from the full PHQ. Each of the 9 items can be scored from 0 (not at all) to 3 (nearly every day), and a total score is obtained by summing the item scores, ranging from 0-27. A score between 0-4 indicates minimal depression, 5-9 indicates mild depression, 10-14 indicates moderate depression, 15–19 indicates moderately severe depression and 20-27 indicates severe depression. If one or two item values are missing from the score, then they can be substituted with the average score of the non-missing items (scored pro-rata and total score rounded to nearest integer). Questionnaires with more than two missing values should be disregarded.[3]
- **Generalised Anxiety Disorder-7 (GAD-7)** – The GAD-7 is a 7-item, self-administered patient questionnaire, which can be used as a screening tool and severity measure for generalised anxiety disorder. A total score is calculated by assigning scores of 0, 1, 2 and 3 to the response categories of ‘not at all’, ‘several days’, ‘more than half the days’ and ‘nearly every day’, respectively and adding together the scores for the seven questions. GAD-7 total score ranges from 0 to 21 with scores of 5, 10 and 15 taken as a cut-off points for mild, moderate, and severe anxiety, respectively. If one or two values are missing from the score, then they can be substituted with the average score of the non-missing items (scored pro-rata and total

score rounded to nearest integer). Questionnaires with more than two missing values should be disregarded. [4]

- **De Jong Gierveld 11-item Loneliness Scale** – The De Jong Gierveld Loneliness Scale consists of 11 items, each with three response options: Yes, More or less, and No. Negatively worded questions (items 2, 3, 5, 6, 9, 10) e.g. ‘I miss having a really close friend’ will be coded as Yes = 1, More or less = 1, and No = 0. Positively worded questions (items 1, 4, 7, 8, 11) e.g. ‘There are many people I can trust completely’ will be coded as Yes = 0, More or less = 1, and No = 1. Researchers can use the scale as a one-dimensional measure of loneliness (sum of all items ranging from 0 (not lonely) to 11 (extremely lonely) provided no more than one item is missing) or choose to use two subscales: emotional loneliness (sum of items 2, 3, 5, 6, 9 and 10; only valid if no missing item data); and social loneliness (sum of items 1, 4, 7, 8 and 11; only valid if no missing item data).
- **Short Form-12 version 2 (SF-12v2)** – This is a health-related quality of life questionnaire consisting of twelve questions that measure eight health domains to assess physical and mental health. Physical health-related domains include General Health, Physical Functioning, Role Physical and Body Pain. Mental health-related scales include Vitality, Social Functioning, Role Emotional and Mental Health. The physical and mental health component scores both range from 0 to 100, where 0 indicates the lowest level of health and 100 indicates the highest level of health measured by the scale. Scoring will be conducted in accordance to the SF-12v2 scoring manual, via the Optum software.[5]
- **Participant circumstances in relation to Covid-19** - whether they are currently social distancing/self-isolation/shielding, the number of people living in household and whether they have felt able to adhere to UK government guidelines on social distancing/self-isolation.

### 7.3 Follow-up

*Table 1: BASIL-C19 Data Collection Schedule*

| BASIL-C19 Statistical Analysis Plan               | Invitation & Study Information Pack | Eligibility | Baseline Questionnaires | Randomisation | 1 -month follow-up | 3- month follow-up | 12 -month follow-up |
|---------------------------------------------------|-------------------------------------|-------------|-------------------------|---------------|--------------------|--------------------|---------------------|
| Consent/Decline for screening/study participation | X                                   | X           | X (re-checked)          |               | X (re-checked)     | X (re-checked)     | X (re-checked)      |
| Demographic questions                             |                                     |             | X                       |               |                    |                    |                     |
| PHQ-9                                             |                                     | X           | X                       |               | X                  | X                  | X                   |
| GAD-7                                             |                                     |             | X                       |               | X                  | X                  | X                   |
| De Jong Gierveld Scale (11 items)                 |                                     |             | X                       |               | X                  | X                  | X                   |
| SF-12v2                                           |                                     |             | X                       |               | X                  | X                  | X                   |
| Resource use                                      |                                     |             | X                       |               | X                  | X                  | X                   |

## 7.4 Other important information

Demographic information will be obtained at baseline and will include a range of sociodemographic variables including age, sex, LTC type, socio-economic status, ethnicity, education, marital status, and number of children.

The PHQ9 will be administered as part of the screening/eligibility assessment in order to assess for risk of self-harm/suicide. The study will record details of any Serious Adverse Event (SAEs) experienced by study participants.

## 8. Analysis

All analyses will be conducted in STATA v16 (StataCorp, [name]), or later, following the principles of intention-to-treat with participants' outcomes analysed according to their original, randomised group, where data are available, irrespective of deviations based on non-compliance.

The trial will be reported according to the CONSORT (Consolidated Standards of Reporting Trials statement) guidelines for pilot and feasibility studies. The flow of participants through each stage of the trial, including reasons for non-eligibility, will be presented in a CONSORT diagram (Ref: Figure 1).

### 8.1 Baseline data

Participant baseline demographics will be summarised descriptively by trial arm and overall, as randomised (Table 2). Continuous variables (e.g. age) will be summarised using n and then either mean and standard deviation (SD), or median, 25th and 75th percentiles, and range as appropriate, and categorical variables, (e.g. sex) using counts and percentages.

No formal statistical significance testing will be done to test baseline imbalances between the intervention arms, but any noteworthy difference will be descriptively reported.

## **8.2 Patient Reported Outcomes**

Patient reported outcomes (PHQ-9, GAD-7, De Jong Gierveld Scale, SF-12v2) at baseline, one and three months will be summarised by group. Mean and standard deviation with the number of observations used in each calculation, will be presented (Table 3). In addition, participant's circumstances regarding Covid-19 will be summarised by group for each time point.

Linear regression will be used to explore differences in the PHQ-9 and De Jong Gierveld Loneliness Scale, adjusting for the baseline measure of the score, between groups at one-month and three-months. The mean difference and a 95% confidence interval will be provided. Model assumptions will be checked prior to analysis.

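### The sample size allows for clustering by support worker but the planned regressions do not, so their intervals are slightly too narrow (about 3% to 6%) on the plan's own ICC

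*SAP*

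**What the plan says.** Section 5 of the SAP states: "The intervention will be delivered by support workers and we can allow for potential clustering by support worker". It takes an ICC of 0.01 and "an average cluster size of 15", and reduces the planned 100 participants to an effective 88, then to at least 70 after 15-20% attrition.

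The comparator described in Section 3 is "care as usual as provided by the participant's current NHS and/or third sector health care providers", plus signposting information. No trial support worker is mentioned for that arm. Section 6 says that participants are "randomised using simple randomisation on a 1:1 basis".

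Section 8.2 says: "Linear regression will be used to explore differences in the PHQ-9 and De Jong Gierveld Loneliness Scale". The only covariate is the baseline value of the score, and a 95% interval is given for the mean difference at one and three months. Section 8.5 repeats the PHQ-9 regression in participants with a screening score of 5 or more and reports 80% intervals. Nothing in Section 8 mentions a support-worker term, clustered standard errors, a sensitivity analysis for clustering, or a reason for ignoring it. The check of model assumptions in 8.2 names neither independence nor a fallback.

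**The concern.** Two sections of the same document make different assumptions about the same data. Section 5 treats participants of one support worker as correlated. Sections 8.2 and 8.5 treat every participant as independent. With any positive ICC, ordinary regression understates the variance of the BA-arm mean, and so the standard error of the difference, which leaves the interval too short. A reader who sees the allowance in Section 5 would expect the reported intervals to reflect it. The intervals may also be read as a guide to plausible effects for the main trial, so their stated confidence level should be right, or the departure should be disclosed.

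**Working it through.** **Inputs.** From Section 5: N = 100, ICC = 0.01, m = 15 per worker, attrition 15-20%. From Section 6: 1:1 allocation. From Sections 3 and 5: support workers deliver the intervention, so clustering is taken to arise in the BA arm.

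**Reproducing the plan's figures.** Design effect DE = 1 + (m − 1) × ICC = 1 + 14 × 0.01 = 1.14. Effective N = 100 / 1.14 = 87.7, stated as 88. With 20% attrition, 87.7 × 0.80 = 70.2, stated as at least 70. Both reproduce, so Section 5 applies the design effect to the whole sample.

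**Effect on the interval for the difference.** With equal arms and equal variances, the ratio of correct to naive variance is (1 + DE) / 2 if only the BA arm clusters, and DE if the design effect applies to both arms. The SE ratio r is its square root. The naive interval is too narrow by 1 − 1/r. Its actual coverage is 2Φ(z/r) − 1, with z = 1.96 for a 95% interval and 1.28 for an 80% interval.

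For BA-arm clustering only: (1 + 1.14) / 2 = 1.07, r = √1.07 = 1.034, and 2Φ(1.96 / 1.034) − 1 = 0.942.

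| Case | Variance ratio | SE ratio | Naive interval too narrow by | Coverage, nominal 95% | Coverage, nominal 80% |
|---|---|---|---|---|---|
| BA arm only, m = 15, ICC 0.01 | 1.07 | 1.034 | 3.3% | 94.2% | 78.5% |
| BA arm only, m = 12 (20% attrition), ICC 0.01 | 1.055 | 1.027 | 2.6% | 94.4% | 78.8% |
| Section 5's whole-sample design effect | 1.14 | 1.068 | 6.3% | 93.4% | 77.0% |
| *Illustrative:* BA arm only, m = 15, ICC 0.02 | 1.14 | 1.068 | 6.3% | 93.4% | 77.0% |
| *Illustrative:* BA arm only, m = 15, ICC 0.05 | 1.35 | 1.162 | 13.9% | 90.8% | 73.0% |

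The last two rows use ICCs that do not appear in the SAP.

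**Scale.** With 40 analysed per arm, and before any gain from baseline adjustment, the 95% half-width is 1.96 × √(2/40) = 0.438 SD. It becomes 0.450 SD (m = 12) to 0.453 SD (m = 15) with BA-arm clustering, and 0.468 SD with the whole-sample design effect.

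**Check by simulation.** With 40 per arm, three BA workers (13, 13 and 14 participants) and ICC 0.01, the ordinary 95% interval covered 94.5%, in line with the first two rows.

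**Number of workers.** About 50 BA participants at 15 each gives 50 / 15 = 3.3, so roughly three or four. This is an inference; the SAP gives no number.

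**The case against.** The strongest reply is that nothing depends on this. Section 5 sizes the pilot to estimate attrition and the SD, not a treatment difference. The primary outcomes are feasibility outcomes, the regressions are described as exploratory, and no test or progression rule in the SAP uses the interval. Section 5's wording is permissive and can be read as a cautious planning discount, not a promise of a clustered model. All of this stands, and it is why the point is minor. It does not remove the mismatch, because the plan neither carries its assumption through nor says why it drops it.

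A second reply concerns the remedy. With three or four workers, a mixed model with a support-worker effect is unstable and its ICC nearly uninformative. For three workers with 13 participants each and a true ICC of 0.01, the usual analysis-of-variance estimate is truncated to zero about 58% of the time, and the exact 95% interval has a median upper limit near 0.70. This also stands, and it rules out such a model as the main remedy.

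A reader might also infer that the plan fails Objective 4 because it does not estimate the ICC. The document does not support that. Objective 4 speaks of sample-size parameters without naming the ICC, and Section 5 names attrition and the SD as what the pilot is sized to estimate.

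**Conclusion.** The inconsistency is real, and its direction is certain for any positive ICC. At the SAP's own ICC the correct standard error is about 3.4% larger than the reported one if only the BA arm clusters, and about 6.8% larger on Section 5's whole-sample design effect. This is a minor point in an exploratory pilot analysis.

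The figures assume equal arms, equal variances, 15 participants per worker and an ICC of 0.01 that also applies to the baseline-adjusted outcome. Attrition reduces the effect. So would the smaller number per worker in the Section 8.5 subpopulation, at the same ICC, so the 80% coverage figures show the effect at its largest under these assumptions.

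A reader might conclude that the intervals are seriously misleading. That would need an ICC well above 0.01, and the SAP gives no ground for one. The rows for 0.02 and 0.05 show sensitivity only.

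**What to change.** In Sections 8.2 and 8.5, keep the planned regression and add beside each interval a sensitivity interval with the BA-arm variance multiplied by 1 + (m − 1) × ICC. Take m from the observed, analysed participants per worker, separately for the subpopulation in 8.5. For arms of n_BA and n_UC, this multiplies the regression SE by √[(DE/n_BA + 1/n_UC) / (1/n_BA + 1/n_UC)], which reduces to √[(1 + DE)/2] for equal arms. Show it at ICC 0.01, to match Section 5, and over a range up to 0.05 labelled as illustrative.

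Report the number of support workers and the participants per worker. Fit a partially nested model (random support-worker intercept in the BA arm only) and report the ICC with its interval only if the number of workers supports it, and say that with about three or four workers the estimate will be very imprecise.

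The cost is a support-worker identifier for BA participants, a few lines of analysis and SAP text, and slightly wider intervals.
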